#### IV. a. 7. Randomization

Eligible participants will be randomly allocated into two groups. The sponsoring organization will own the randomization process. A unique random number will be generated for each member. The members will be randomly allocated each month to each arm. Restriction (e.g., blocking, stratification, matching) will be leveraged as required.

#### IV. a. 8. Interventions by Treatment Arm

##### **Intervention Group:**

As described in above, 100% of the members randomized to the intervention treatment arm each month will be eligible to receive the CM/CC program. All eligible members are loaded into software to determine if the member is operationally qualified for outreach (e.g., not identified on ‘do not call’ list, currently enrolled in health plan, not qualified for other programs, valid telephone number, etc.). Based on an initial capacity study, it was originally estimated that CM/CC staff would only have capacity to manage approximately 20,000 unique members annually. However, operational capacity was increased to 35,718 unique members in 2018.

Members who are qualified for the program will receive a pre-engagement message either by mail or email. The pre-engagement message introduces CM/CC services to the member. The message also informs the member that they will receive a call about the program or that they could place a call to the inbound RN Case Manager phone line to discuss services.

There are two methods for outbound telephonic outreach that are used within the program.

1. A non-clinical staff specialist initiates the first contact with the member leveraging auto-dialer technology. Upon contacting the individual, the staff specialist validates that the individual is the member of interest and transfers the member to a registered nurse (RN). If the member is unable to speak for an extended period, the staff specialist schedules an appointment with the member and the RN at the member’s convenience. If the member’s spoken or preferred language is not English, the staff specialist will engage an external translator service, “Language Line Solutions” and will document in the member’s case record the primary language for subsequent outreach. If necessary, the RN will also leverage “Language Line Solutions”.

An RN Case Manager will directly dial the member’s phone number and attempt contact. Once contact is made, a similar process is followed as above. The RN Case Manager will also offer to immediately begin working with the member to identify and reduce clinical risks.

The method used is based on RN Case Manager capacity given daily needs of existing case load and incoming referral volume. If the RN Case Management team has adequate capacity they will perform the direct dial method, which is preferred. If capacity is limited, the CM/CC program will leverage the auto-dialer and non-clinical staff specialist as the first point of contact.

If the member does not agree to participate, or if during the initial outreach call it is determined by the staff specialist that the member is not clinically eligible for the program, the program referral is rejected and the appropriate reason is documented. Additionally, the member can be excluded from additional calls in the future via an Opt-Out process if requested by the member.

If the member is not reached during the initial outreach call, a second call will be placed within 5 business days. Two additional outreach attempts will be attempted before the "No Contact Letter" letter is mailed to the member. After 30 days, the process of attempted outreach repeats.

#### **Stage 1 Program – Active 11/01/2015 to 10/31/2019**

Upon successful telephonic contact with the member, the RN provides the member with an overview of the Stage 1 intervention, advises the member of their rights and responsibilities, provides the member with their direct phone number (with private voice mail) and hours of operation, provides the member with the 24 hour, general helpline number (available to all plan members), confirms the name and address of the member's primary managing physician(s), and confirms verbal agreement by the member to participate in the program. During the first call, the RN also engages in the following activities: 1) completes a self-reported medication review (supplemented with administrative data if applicable), 2) completes the Barriers to Care Adult Clinical Assessment of current conditions for the member focused on risks for adverse health events, gaps in care and barriers to care, , 4) addresses any urgent care coordination needs (e.g., member is unable to fill prescriptions following discharge from hospital), 5) develops a consumer-centric case management plan, and 6) informs the member of the next outreach timeframe. The initial assessment process outlined above may require multiple phone calls over the course of several days depending on the unique scenario. If a member misses a scheduled appointment, the RN will send the Missed Appointment Letter. In cases where a member is newly discharged from the hospital, the Discharge Assessment will be completed in place of the Barriers to Care Assessment (which may still be used at a later time). The Discharge Assessment was developed to help the RN Case Manager quickly identify and reduce re-admission risks. The Discharge assessment focuses on medication changes/risks, ensuring follow-up with a provider within 7 days of discharge or per the discharge instruction timeline, symptom management, access to DME, and other common post-discharge needs.

The second contact generally occurs within seven days or less. In general, the maximum timeframe of outreach is 30 days after the last contact with the member. Additional outreach may occur as needed at the nurse's discretion depending on closure of gaps in care. If during the initial call or subsequent calls, an interpreter is needed to ask questions, complete assessments or cover educational mailings, the clinician makes use of the "Language Line Solutions" interpreter service and notes on the member's case record their primary spoken language. If necessary, the initial Barriers to Care Adult Clinical Assessment can be updated. Furthermore, subsequent inpatient discharges can retrigger the capture and reprioritization of inpatient-related post-discharge care coordination opportunities since this is an event driven process.

Members are contacted at minimum monthly until all clinical risks and opportunity (gaps in care) are closed. Clinical risks are prioritized via the consumer centric case management plan. Clinical risk reduction focuses on improving medication adherence, medication reconciliation, improving condition-based measures and outcomes, addressing psycho-social needs, and intensive transition of care support following an inpatient admission. RN Case Managers refer cases to MDs or Pharmacists for case consultations as needed. MDs maintain 'open office hours' with Behavioral Health clinicians for Behavioral Health case consultation, when needed. MD's will also coordinate with local health plan Chief Medical Officers and treating providers to develop customized plans for addressing members with high clinical risks who are difficult to engage. Social workers are also available to RN Case Managers to identify resources to address barriers to care. In cases where members cannot be reached, the RN Case Manager may perform a review of available clinical data

within the system for the members. If clinical risks are identified, a referral will be made to the MD to evaluate for peer-to-peer engagement with the member's primary care provider to socialize identified risks. CM/CC RN Case Managers may also refer members to additional services such as help finding a Behavioral Health Provider, Behavioral Case Management services via Life Solutions and smoking cessation via Quit For Life. A clinical risk is considered addressed when (1) an identified gap in care has been closed through change in treatment or behavior achieved by communication with member/provider (2) an identified gap in member education is addressed by the RN and member demonstrates understanding (3) the intervention is assessed and determined there is no gap and (4) when all appropriate steps have been taken (i.e. exhausted) but the gap is unable to be resolved.

During program management, members may be referred to Transplant Resource Services, the End Stage Renal Disease program, the Chronic Kidney Disease program, the Cancer Support program or the Heart Failure Disease Management program. When a member is referred to these programs they will also be transferred to the program and no longer directly serviced by the CM/CC program. Results for these programs, for both intervention and control groups, are included in the aggregate RCT results.

Members are actively managed based on the determined outreach schedule until they (1) leave insurance, (2) expire, (3) refuse to continue to participate in the program, (4) are lost to follow-up or (5) graduate the program due to clinical risks being resolved. Graduating members will be re-enrolled following a subsequent high-risk acute inpatient discharge or direct referral from the member or the member's physician.

#### **Stage 2 Program – Active 11/01/2015 to 10/31/2019**

At any time, if the RN determines that the ongoing management of the member will take longer than the approximate 60-day intervention period for Stage 1 based on open gaps in care (measured via a proprietary scoring tool) and the combined clinical knowledge of the RN and Medical Director, the member may be promoted to more intense case management via Stage 2. If the member is identified for promotion to Stage 2, the RN contacts the member and provides them with an overview of the Stage 2 process, advises the member of their rights and responsibilities, notifies the member that they will receive the "Stage 2 Welcome Letter" which includes the patient rights and responsibilities as well as the Advanced Directives Brochure, and documents agreement by the member to participate in the program. The Stage 2 protocols for members who decline mirror those used in Stage 1.

After enrollment in Stage 2, the identified primary managing physician(s) is mailed a "Physician Welcome Letter" indicating that their patient has been enrolled in the Stage 2 program. The letter provides a general overview of the Stage 2 program and notifies the provider that nurse case managers and/or medical directors may contact them to support the provider's treatment plan and coordinate services. Upon promotion to the Stage 2 program, the RN addresses any urgent care coordination needs and completes the Comprehensive Barriers to Care Adult clinical assessment or the new Barriers to Care Adult clinical assessment which is tied to the earlier assessment; however, the comprehensive version has more extensive required elements to provide a more holistic view of the member's risks for adverse health events, gaps in care and barriers to care.

#### **CHW CM/CC – Active 11/01/2015 to 7/1/2017**

In selected markets for defined time periods, members randomized to the intervention arm also received an enhanced version of the CM/CC intervention that included in-home care management support from non-clinical Community Health Workers (CHW). A CHW was anticipated to be helpful to ensure that this population understood the general health insurance process, understood the vital importance of establishing a relationship with a Primary Care Physician (PCP), and was assisted with community resources as necessary in order to optimize their health care experience.

In general, the outreach protocol for this enhanced CM/CC intervention mirrored the outreach protocol described previously. However, there were a few differences. The primary difference was that the CHW performed the outreach call and scheduled a home visit with the member if they resided within the CHW's service area. In addition, each member was assigned to a Community Care Team which was comprised of an

on-site CHW, a telephonic RN, and other telephonic specialists as needed. The Community Care Team was accountable for end-to-end integrated person-centered care management of all members to whom they were assigned. All members were assigned to one on-site CHW. Following contact with the CHW, individuals identified with more complex needs were also assigned to a telephonic clinician from the Community Care Team for longitudinal interventions.

As members were enrolled in the program, the Community Care Team also ensured that each member was assigned a PCP, which may have been a specialist, if they had not yet chosen one or wished to change providers. Each member was strongly encouraged and steered towards the optimal use of the PCP as the medical home for community-based health and preventive services. As this link was established, the team involved the PCP in the plan of care (POC) development process and reinforced their treatment plan in accordance with the evidence-based clinical guidelines that form the foundation of the program.

The CHW tracked the status of all scheduled home visit attempts. In the case of an unsuccessful home visit, the CHW made three call attempts to reschedule the home visit. A field visit was attempted on members who were unable to be reached by phone by the CHW. During the home visit, the CHW completed the Access to Care questionnaire and the PHQ-9 survey. The information documented by the CHW included but was not limited to: primary care physician visits, transportation needs, medication concerns, and home health and durable medical equipment needs. If the member was recently hospitalized, the CHW completed the Post Hospitalization assessment.

If during the initial outreach call by the CHW, it was determined that the member was not within the service area, or if member refused a home visit, but agreed to talk over the phone, the CHW completed the Access to Care questionnaire and the PHQ-9 survey during the initial outreach call. If the member was not able to talk immediately, a follow-up telephone call was scheduled to continue the conversation.

During subsequent telephonic contact with the Community Care Team clinicians, the assigned RN may have also completed the Adult Core assessment or the SF-12 survey based on clinician judgment. Members were managed longitudinally until three months after they were no longer identified as eligible for the program.

**Control Group:** It is important to note that throughout the study period, the CM/CC program will continue to be available to all commercial health plan members (including the control group in the current QIS) who are 1) discharged from an inpatient facility and identified as being at high risk for readmission and 2) identified via physician referral or self-referral as someone who may benefit from care coordination. It is expected that approximately 5-10% of the 100,000 members randomized to the control group will receive the CM/CC intervention. Furthermore, engagement in other programs will be monitored in order to determine if stratification is necessary since both treatment arms also have access to other care or disease management programs, such as Transplant Resource Services, the End Stage Renal Disease program, the Chronic Kidney Disease program, the Cancer Support program, or the Heart Failure Disease Management program.

#### **IV. b. Data Analysis and Data Monitoring**

*Primary Data Analysis:* All analyses will be based on administrative data. In order to address claims lag, the administrative data will be pulled four months following the end of each intervention period.

Univariate analyses (standardized differences) will be used to test for baseline differences between the treatment groups. Any statistically significant differences in baseline characteristics will be controlled for in the multivariable models assessing the study outcomes. Unless otherwise noted, all tests will be two-sided tests with  $\alpha = 0.05$ . Model diagnostics will be utilized to evaluate the need to address outliers.

The primary study outcomes include the following:

- a 2.5% reduction in acute inpatient admissions
- a 2.5% reduction in 30-day all-cause readmissions
- a 2.5% reduction in emergency room visits
- a 2.5% increase in primary care physician visits
- a 2.5% increase in specialist physician visits

Utilization metrics will be compared between intervention groups at 12, 24, 36 and 48 months following randomization using a repeated measures Poisson or negative binomial regression model. Zero-inflated models will be utilized if appropriate. The Cox proportional hazards test will be used for all cause 30-day readmission. Results will be reported in aggregate, as well as stratified by year of randomization.

*Secondary Data Analyses:* The study will also explore numerous secondary outcomes that were not powered, but that are important for continuous quality improvement – the primary goal of a QIS. Examples include the following:

- Total cost of care: Utilization and cost will be evaluated for all service categories to identify hypotheses for continuous quality improvement.
- Variable cohort definitions:
  - A “once qualified, always qualified” definition will be used to evaluate the long-term impacts of the program after a member is no longer identified by the monthly refresh of the algorithms. This mirrors a more academic approach to the measurement of outcomes.
  - An “operational” definition will include members until 120 days after they are no longer actively identified by the monthly refresh of the algorithms. This view is designed to drive continuous quality improvement.
- Health plan type: The impact of the program among the Individual Exchange population compared to the traditional Fully Insured population will be evaluated.
- Disease: The comparative effectiveness of the program by disease will be evaluated to drive continuous quality improvement and to identify hypotheses for new program offerings. .
- Access to Other Programs: Qualification for other programs will be monitored in order to determine if stratification is necessary by program qualification for other programs since both treatment arms also have access to other care or disease management programs, such as Transplant Resource Services, the End Stage Renal Disease program, the Chronic Kidney Disease program, the Cancer Support program, or the Heart Failure Disease Management program.

*Study Timeline:* The proposed timeline for the QIS includes the following dates & activities:

10/01/2015 IRB Submission  
10/08/2015 Program effective in tech platform  
10/19/2015 Dialer team stages referrals  
11/01/2015 **Intervention begins.** Members start receiving outreach  
12/31/2015 1st monthly operational metrics report available  
01/31/2016 1st monthly operational leading indicator report available  
01/31/2016 1st monthly outcomes report (notifications) available  
05/31/2016 1st monthly outcomes report (claims) available  
06/01/2016 On-site CHW model expanded to 12 states  
12/31/2016 Individual exchange plans end except for NY and VA  
07/01/2017 CHW intervention ends  
10/01/2017 Randomization moved from 50/50 percentage split to 40/60  
09/01/2018 Engagement of inpatient referrals begin  
10/31/2019 **Intervention ends**

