- a. *Challenge the current state via a pragmatic randomized controlled trial with health plan members as the unit of randomization.* Randomly allocate approximately 705,000 high-risk members into two groups over a four-year period. Compare rates of utilization including acute inpatient admissions, readmissions, ER visits, PCP visits, and specialist visits. This knowledge will allow decision makers to minimize uncertainty as they evaluate opportunities to expand the program.
- b. *Investigate the comparative effectiveness of the approaches to improve health outcomes.* The identification of an improved approach to the expansion of the CM/CC program could lead to reduced complications and improved health outcomes.

The long-term aims of the proposed study are to disseminate the study's findings. The authors anticipate that the communication of positive study results would result in the expansion of the CM/CC model to the entire high-need, high-cost population and ultimately, lead to improved health outcomes for members with high costs and utilization.

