### **III. Criteria for Subject Selection**

#### **III.a. Baseline Studies**

**III.b. Number of Subjects:** As of July 2015, there were 4.5 million program eligible members. Among the eligible population 102,014 (point prevalence of 2.28%) were identified via a proprietary administrative algorithm as being high-need, high-cost (i.e., identification in the top five percent of spend and utilization in year 1 and year 2, based on member characteristics in Year 1). Since the inclusion algorithm will be refreshed monthly for 12 months, modelling based on 2014 data suggests that approximately 200,000 unique members will be identified as being at high-need, high-cost, and included in the randomization frame, over the first 12 months of the QIS.

156 **III.c. Gender of the Subjects:** Participants are expected to be 60.1% female.

157  
158 **III.d. Age of the Subjects:** The age range of the sampling frame will be limited to ≥18 years of age.  
159 Participants are expected to have an average age of 47.5.

160  
161 **III. e. Racial and Ethnic Origin:** Racial and Ethnic data are only self-reported for 3.5% of the commercial  
162 population: 20.7% African American, 1.9% American Indian/Alaskan Native, 4.8% Asian, 64.5% White, Non-  
163 Hispanic, 6.6% Hispanic, 0.0% Native Hawaiian or Other Pacific Islander, 1.2% Other, 0.3% Declined to  
164 Answer, and 0.0% Unknown to Member or Uncoded. The distribution of race/ethnicity of the high-need, high-  
165 cost population is expected to mirror the commercial population.

166  
167 **III. f. Inclusion Criteria:** The commercial Fully Insured population members in all states are represented in  
168 the initial population prior to condition identification. This is also inclusive of the Individual Public Exchange  
169 business, part of Health Care Reform, also known as ObamaCare. The age range of the sampling frame will  
170 be 18 or greater years of age. Members must also be actively enrolled in the health plan as of the date of  
171 randomization. Study participants will be identified via proprietary administrative algorithm as being at high-  
172 need, high-cost.

173  
174 **III. g. Exclusion Criteria:** The population sampled will exclude pregnant women, individuals prescribed  
175 medications for infertility, members with evidence of dementing disorders, and members under the age of 18  
176 years old. Members in the following products and plans will also be excluded:

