## IV. a. 2. Justification of Study Design

IV. a. 2. Justification for a pragmatic design: Pragmatic, or naturalistic designs, are designed to evaluate how a technology works in normal or usual practice and take into account patient and provider variations and can range from experimental to quasi-experimental studies. Pragmatic experimental designs retain random allocation to treatments to minimize bias, but offer fewer restrictions in how patients are recruited and followed after randomization, thus increasing external validity and generalizability. Pragmatic experimental designs have been used previously to evaluate strategies to promote the adoption of low-risk public health recommendations, such as CMS's evaluation of the Health Support pilot (i.e., Chronic Care Improvement Program) or the National Health Service's (NHS) evaluation of the impact of fecal occult blood test (FOBT) screening for colorectal cancer.

Generally, experimental designs are structured so that recruitment precedes randomization in order to evaluate the efficacy of an intervention; however, randomization occurs before recruitment (i.e., enrollment) in pragmatic methodologies which are designed to evaluate the effectiveness of an intervention. The use of the pragmatic design balances the goals of internal and external validity.

IV. a. 3. Sample Size: The study was powered for acute inpatient admissions, the most restrictive outcome, using the sample size estimation for trials of recurrent events in SAS. A baseline study of patients meeting the high-need, high-cost criteria suggests that a total sample size of 171,454 (85,727 per treatment arm) would provide the study with  $\geq 80\%$  power to detect the following intent to treat differences between treatment groups at an  $\alpha=0.05$  over the first 12 months of the four year study:

- a 2.5% reduction in acute inpatient admissions
- a 2.5% reduction in 30-day all-cause readmissions
- a 2.5% reduction in emergency room visits
- a 2.5% increase in primary care physician visits
- a 2.5% increase in specialist physician visits

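### Covariates are chosen by significance of baseline differences, under a rule that conflicts with its own test and leaves prior-year utilisation and randomization period unspecified

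*Protocol*

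**What the plan says.** Protocol IV. b, Primary Data Analysis, has three consecutive sentences on this. The baseline check: "Univariate analyses (standardized differences) will be used to test for baseline differences between the treatment groups". Its consequence: "Any statistically significant differences in baseline characteristics will be controlled for in the multivariable models assessing the study outcomes". The general testing rule: "Unless otherwise noted, all tests will be two-sided tests with" α = 0.05. No cut-off is given for a standardized difference, and no covariate is named for any outcome model.

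Other places that bear on it:

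- IV. a. 3 (Sample Size) powers the trial on 85,727 members per arm for "a 2.5% reduction in acute inpatient admissions".
- III.b expects that "approximately 200,000 unique members will be identified as being at high-need, high-cost" in the first 12 months. The purpose section gives the four-year target: "Randomly allocate approximately 705,000 high-risk members into two groups over a four-year period".
- III.b and IV. a. 6 show that eligibility is built on Year 1 characteristics and on spend and utilisation in the previous year.
- IV. a. 7 (Randomization) permits blocking, stratification or matching if needed, and names no factor.
- The Study Timeline records, for 10/01/2017: "Randomization moved from 50/50 percentage split to 40/60".

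**The concern.** Among members randomized at one fixed ratio, a significant baseline difference is a chance event. It says nothing about whether the characteristic predicts the outcome. A rule that adjusts on significance therefore selects on the wrong property: a strong predictor that happens to balance stays out, and a weak one that happens not to balance goes in. At this sample size the flagged differences can also be trivially small.

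The two sentences also conflict. A standardized difference measures size and does not test significance. Two analysts following the text could fit different primary models.

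At stake is precision in a trial aimed at a 2.5% effect, and a primary model whose terms are not known until the baseline data are examined. For the four-year aggregate there is a separate issue: the allocation ratio changed partway, so arm and randomization period are associated by design and not by chance.

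**Working it through.** **The plan's own figure.** IV. a. 3 gives a 20% as-treated reduction, 20% engagement, 6.5 months engaged and 10.6 months at risk. The diluted effect is 0.20 × 0.20 × 6.5/10.6 = 2.45%, which matches the stated 2.5%. The 85,727 per arm cannot be reproduced, because the base rate and dispersion are not given. Solving the negative binomial formula backwards:

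n = (1.960 + 0.842)² × (1/μ₀ + 1/μ₁ + 2k) / ln(0.975)²

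With n = 85,727 the bracket is 7.00, so 1/μ + k averages about 3.50 per arm.

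**Reading 1: a p-value rule.** The smallest standardized difference significant at two-sided 0.05 is 1.96 × √(1/n₁ + 1/n₂).

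| Sample | Smallest flagged difference (SD) |
|---|---|
| 85,727 per arm | 0.0095 |
| 100,000 per arm | 0.0088 |
| 352,500 per arm (705,000 at 1:1) | 0.0047 |
| 705,000, if all at 40/60 | 0.0048 |

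For sex (60.1% female, III.c), 0.0095 SD is 0.0095 × √(0.601 × 0.399), or about 0.46 percentage points. Each characteristic has a 5% chance of entering. Among 20 independent characteristics one is expected to enter, and the chance of at least one is 1 − 0.95²⁰ = 64%. Sample size does not make chance imbalances more frequent; it makes the flagged ones smaller.

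**Reading 2: a size cut-off.** With an assumed cut-off of 0.1, the threshold lies 0.1/√(2/85,727) = 20.7 standard errors out, or 42 at 352,500 per arm. Chance imbalance would select almost nothing.

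**Precision forgone.** Assume that prior utilisation explains a share R² of the outcome variance. Power when it is always adjusted for is Φ(2.8016/√(1 − R²) − 1.96). The values for the written rule (reading 1) come from a simulation of 4 million draws in the large-sample normal limit.

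| R² (assumed) | Power, always adjusted | Power, written rule | Type I error, written rule | n per arm for 80% if always adjusted |
|---|---|---|---|---|
| 0.05 | 82.0% | 80.3% | 0.0486 | 81,441 |
| 0.10 | 84.0% | 80.5% | 0.0471 | 77,155 |
| 0.20 | 88.0% | 80.9% | 0.0445 | 68,582 |

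**Ceiling on R².** Covariates can explain overdispersion (k) but not the Poisson part (1/μ). The largest possible variance reduction is 1 − (average 1/μ)/3.50, with μ₀ = annual rate × 10.6/12 and μ₁ = 0.975 μ₀. The annual rates are assumptions.

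| Admissions per year | Average 1/μ | Ceiling |
|---|---|---|
| 0.35 | 3.28 | about 6% |
| 0.40 | 2.87 | about 18% |
| 0.50 | 2.29 | about 34% |

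**Randomization period.** From 11/01/2015 to 09/30/2017 is 23 months at 50/50; from 10/01/2017 to 10/31/2019 is 25 months at 40/60. Assume even monthly accrual. The share of the 40% arm randomized late is 0.4 × 25/(0.5 × 23 + 0.4 × 25) = 46.5%. For the 60% arm it is 0.6 × 25/(0.5 × 23 + 0.6 × 25) = 56.6%. The gap is about 10 percentage points, or about 0.10/0.497 = 0.20 SD. Anything that drifts with calendar time inherits part of this gap. Plan type is one example: the timeline ends most Individual Exchange plans on 12/31/2016, inside the 50/50 period.

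**The case against.** The strongest reply is that naming covariates is normal work for a statistical analysis plan, which is not shown. The text says significant differences will be adjusted for; it does not say that only those will be. IV. a. 7 also leaves room for stratification. This stands in part: prior-year utilisation is not barred, and the fair statement is that it is not pre-specified. It does not rescue the rule, because the protocol itself states one and states it inconsistently.

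A reader might infer that the rule biases the treatment effect or inflates type I error because the model is chosen after seeing data. The documents do not support that. Selection uses baseline data only and is blind to outcome. Under valid randomization the rate ratio is not biased, and overall type I error under the rule falls slightly below 0.05.

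A reader might also assume a large gain, such as a correlation of 0.3 to 0.5 that cuts variance by 9 to 25%. No correlation is given. IV. a. 6 reports that 36% of members in one year's top 5% stay there the next year. Against a 5% base rate that is about sevenfold, so prior use is prognostic in general. It does not show how prior admissions predict admissions within a cohort already selected on high use, where range restriction should weaken the relation. The Poisson ceiling excludes part of that range at some base rates compatible with the stated sample size.

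Results stratified by year of randomization are planned and largely separate the two allocation ratios. That helps the yearly results but does not define the aggregate model.

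**Conclusion.** The point holds as a badly fixed rule. The two sentences cannot both be followed as written. Under either reading, the choice of covariates is unrelated to prognostic value, and prior-year utilisation would usually stay out (about 95% of the time under the p-value reading).

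The cost is lost precision and a primary model that is not fixed in advance. Its size is uncertain and may be small: about 2, 4 or 8 points of power above a nominal 80% for assumed R² of 0.05, 0.10 or 0.20, with R² capped near 6%, 18% or 34% at assumed base rates of 0.35, 0.4 or 0.5 admissions per year. These figures rest on the negative binomial reconstruction of the stated sample size.

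The four-year aggregate is the exception to the statement that imbalance is chance. There the ratio change links arm to period, so period belongs in the model whatever a baseline test shows. The documents do not allow the size of any resulting distortion to be estimated. The change is worth making, but the trial's validity does not hang on it.

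**What to change.** Delete the sentence that adjusts for significant baseline differences, and keep standardized differences for description only. Pre-specify the same covariates for every outcome model:

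- the member's prior-period count of that outcome, with an offset or indicator for months of prior enrolment, since III.f requires active enrolment only at randomization;
- age, sex and plan type (Individual Exchange or traditional Fully Insured);
- the identifying algorithm (high-need, high-cost or inpatient risk), with its score if available;
- randomization period, at least before and after 10/01/2017, and preferably the monthly cohort.

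The cost is a short protocol edit, slightly more analysis work, and handling of members with incomplete prior enrolment. The analyses already rest on administrative data, so no new data collection is foreseen.
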